#### Other: Environmental light exposure and melanopsin function

The environmental light exposure measured with actigraphy (Geneactive) was analysed using RM-ANOVA (2 lights x 6 time points) in IBM SPSS Statistics (version 29).

Baseline melanopsin function (6sPIPR) in both PD light intervention groups was compared to an age-matched healthy control group (n=10) using One way-ANOVA with Bonferroni corrections in IBM SPSS Statistics (version 29).

Detailed description of all the tests conducted to derive primary, key secondary and secondary outcome measures

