### Exploratory:

- Change from baseline to week 4 and week 6 in mean PDQ-39 total score, BDI-II total score and MDS-UPDRS total and motor scores

During the 6 weeks of the study duration, participants wore an actigraphy wristwatch (GENE Active V3.1, Activinsights Ltd, UK) to record environmental light exposure.

- The daytime light exposure levels were adjusted as per the sunrise and sunset times given by the geodetic calculators provided Geoscience Australia (<https://geodesyapps.ga.gov.au/sunrise>) for Brisbane Australia.
- The weekly average of light exposure were compared between the groups over the six weeks of the study period
- For adherence, the illuminance data were also used to verify the ambient light level during the salivary sample collection

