## Supplementary Methods

### Statistical analyses

#### Outcome measures

The plan for analysis of the data was decided upon before the commencement of the analyses and was formulated by the Researchers based on scientific rather than statistical grounds. Furthermore, and given the longitudinal nature of the data it was decided to fit a mixed model in each case, with a random intercept for each participant. Time in all cases was fitted as a categorical fixed effect.

Time and group were fitted as fixed effects along with their interaction. Participant ID was fitted as random effect with the inclusion of age, disease stage, disease duration and LEDD (Levodopa dosage).

The model was fitted for all outcome variables. Following the analyses, the resultant models objects were processed in order to derive appropriate estimated marginal means. All mixed model analyses was performed in R using “lmerTest”, “tidyverse”, “flextable”, “openxlsx”, “janitor”, and “emmeans”, and custom written codes in R.

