#### Actigraphy: Control of environmental light exposure, DLMO and light therapy adherence

A fully charged wrist-worn actiwatch (GENE Active V3.1, Activinsights Ltd, UK) was provided to participants at the start of each time point (3 watches per participant). Each watch was pre-configured to collect data on light exposure levels and physical activity over 14 days at a sampling frequency of 50 Hz (50 readings per second). Participants were asked to wear the actiwatch continuously except for when showering or swimming, and to record the non-wear times (in the sleep diary). Data from the actiwatch were extracted and analysed using GENEActiv software to average the data in 60 s epochs. A correction factor was applied to the absolute illuminance values to obtain accurate light exposure levels recorded by the actiwatch.

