### 6.2. Data analysis and statistical methods

Descriptive statistics will be calculated for demographic characteristics for the full study cohort and by light therapy study group. Categorical variables will be summarised as percentages and continuous variables will be summarised by medians, means with standard deviations. Participants will be analysed according to the light therapy group as randomised. Analysis will follow an intention to treat principle with missing values accounted for in the statistical model. Mixed models will be used to account for the longitudinal nature of the data, using intervention group, time point (baseline, week 4 and week 6) and interactions as explanatory variables to the primary, secondary and exploratory outcome measures in R applying packages. The fitted mixed models will be used in *post hoc* analyses with respect to group and time point to explore potential differences due to these two variables and their interaction. The mixed models will be adjusted for baseline characteristics including age, sex, Hoehn and Yahr disease stage, PD duration and levodopa equivalent daily dosage (LEDD).

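### The weekly light-exposure comparison uses a 2 x 6 RM-ANOVA that drops any participant with a wholly missing week, and no missing-week rule or analysed n is given; the trial's own mixed model would keep them

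*Combined protocol and SAP*

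**What the plan says.** In the Supplementary Methods, under Other: Environmental light exposure and melanopsin function, the actigraphy light data were "analysed using RM-ANOVA (2 lights x 6 time points) in IBM SPSS Statistics (version 29". The Endpoints section adds, in a paragraph printed after the exploratory endpoints: "The weekly average of light exposure were compared between the groups over the six weeks of the study period".

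The actigraphy section states that a charged watch "was provided to participants at the start of each time point (3 watches per participant", each set to record for 14 days. Participants were to log non-wear in the sleep diary. The caption of Figure S1 describes group means with 95% CIs over the six weeks but gives no n. I found no minimum-wear rule, no rule for a missing week and no imputation.

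For the longitudinal outcomes the documents take a different route. Protocol section 6.2 says: "Analysis will follow an intention to treat principle with missing values accounted for in the statistical model". It also says: "Mixed models will be used to account for the longitudinal nature of the data". The scope of those models is given as "interactions as explanatory variables to the primary, secondary and exploratory outcome measures in R applying packages". The supplement's Outcome measures subsection repeats the approach: "given the longitudinal nature of the data it was decided to fit a mixed model in each case, with a random intercept for each participant".

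**The concern.** A conventional repeated-measures ANOVA takes one row per participant with all six weekly values filled, and a participant with one empty week leaves the analysis altogether. That is a property of the method, and nothing in the documents describes a step that would prevent it. The weekly light averages are longitudinal data on randomised participants, yet they are not given the in-model handling of missing values that the same trial uses for its outcomes.

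What is at stake is limited. The comparison bears on whether ambient light differed between arms and could therefore contribute to the treatment contrast. A non-significant test is weak evidence of similar exposure in any case, and weaker still on a reduced set of unknown size. An interval for the between-arm difference would tell the reader more. No primary or secondary analysis depends on this result.

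**Working it through.** **No figure to reproduce.** The documents give no n, power or missing-data count for the light analysis, so the size can only be illustrated.

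**Inputs**
- Participants: 57, the Table S1 baseline count (27 Day Mel + 30 Enhanced Mel), used as a stand-in for those with actigraphy.
- Weekly values needed per participant: 6 (the 2 x 6 design).
- Watches per participant: 3, each covering 14 days, so one lost watch removes two of the six weeks.
- Missing rate: not given. Assumed 2%, 3% or 5%, unrelated to arm.

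**Pattern A: whole watches lost independently, rate q.** The proportion kept is (1 - q)^3.
- q = 0.02: 0.98^3 = 0.941; 5.9% dropped; 57 x 0.941 = 53.6 kept
- q = 0.03: 0.97^3 = 0.913; 8.7% dropped; 57 x 0.913 = 52.0 kept
- q = 0.05: 0.95^3 = 0.857; 14.3% dropped; 57 x 0.857 = 48.9 kept

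**Pattern B: single weeks lost independently, rate p.** The proportion kept is (1 - p)^6.
- p = 0.02: 0.98^6 = 0.886; 11.4% dropped; 57 x 0.886 = 50.5 kept
- p = 0.03: 0.97^6 = 0.833; 16.7% dropped; 57 x 0.833 = 47.5 kept
- p = 0.05: 0.95^6 = 0.735; 26.5% dropped; 57 x 0.735 = 41.9 kept

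At equal rates the two patterns lose the same share of weeks. They differ only in how many participants those weeks are spread over. A mixed model keeps every participant with at least one valid week under either pattern.

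**Precision under pattern B.** A generalised least squares calculation gave the standard error of the group difference. It used 27 v 30 participants, week and group effects, compound symmetry with intraclass correlation 0.3 to 0.7, weeks missing completely at random, and 200 simulated patterns. The complete-case standard error was about 6% larger than with all available weeks at p = 0.02, and 16-17% larger at p = 0.05.

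**Precision under pattern A.** The loss is smaller. Relative to complete data, the complete-case standard error grows by about 1/sqrt(0.941) = 1.03 at q = 0.02 and 1/sqrt(0.857) = 1.08 at q = 0.05. A mixed model on the available weeks cannot do better than complete data, so its gain is at most about 3% to 8%.

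**The case against.** The strongest reply is that light exposure is an environmental check. Protocol section 2.2 does not list it as an outcome, the supplement files its analysis under Other, and the mixed-model statements concern outcome measures. This stands. A reader might infer a clear protocol breach, particularly because the comparison is printed under the Exploratory heading, but the documents do not support more than an inconsistency of approach.

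It can also be said that no missing watch-week is reported anywhere, that the non-wear foreseen is for showering or swimming, and that scheduled watch exchange for download and recharge guards against loss. A partly worn week can still yield an average. All of that stands, and it is why the size is conditional.

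Three further readings are tempting and should not be made:
- **Loss mainly in the Enhanced Mel arm.** In Table S1, PDQ-39 counts at week 4 are 26 of 30 in Enhanced Mel and 27 of 27 in Day Mel. Those are questionnaire counts. For the pupil response in Figure S2, week 4 has 25 and 25, from 27 Day Mel and 28 Enhanced Mel, so both arms lost data. There is no actigraphy count by arm.
- **Violation of sphericity.** The trial's random-intercept model implies compound symmetry, which is at least as restrictive, so changing to it is no cure. The between-group main effect does not depend on sphericity.
- **Every other repeated measure has a mixed model.** This is not established for the pupil response, for which the supplement names only a baseline one-way ANOVA against healthy controls.

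Finally, a 2 x 6 design already contains a group-by-week interaction, and Figure S1 displays the arms across all six weeks, so the intervention and wash-out periods are not hidden. What is not described is an interval for the between-arm difference in each period.

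**Conclusion.** The point holds as a small, free improvement to a supporting analysis. The stated method discards participants with a wholly missing week, no rule or count lets the reader judge how many, and the trial already has a model that would retain them.

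Of 57 participants, about 54, 52 or 49 would remain if 2%, 3% or 5% of watches were lost, and about 50, 47 or 42 if the same share of weeks were lost singly. The range of 11% to 26% dropped should not be read as the expected loss: it belongs to independent single-week gaps, and loss of whole watches roughly halves it. All rates are assumptions, as are the use of 57 and the independence of losses. If no week was wholly missing, no one was dropped and only the reporting gap remains.

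**What to change.** Fit the trial's existing mixed model (group, week, group x week, random participant intercept) to all available weekly averages. From that model, report the between-arm difference in light exposure with 95% CI, averaged over weeks 1-4 (intervention) and weeks 5-6 (wash-out) separately. Base any statement that ambient light was comparable on those intervals, and not on a non-significant test.

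Give n per week and arm, and state when a week counts as missing. The mixed model still assumes that missingness is explained by the observed data, so the counts are needed in either case.

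The R packages for fitting the model and deriving marginal means are already named in the supplement. The cost is one re-run on existing actigraphy data and a line or two of reporting.

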#### Actigraphy: Control of environmental light exposure, DLMO and light therapy adherence

A fully charged wrist-worn actiwatch (GENE Active V3.1, Activinsights Ltd, UK) was provided to participants at the start of each time point (3 watches per participant). Each watch was pre-configured to collect data on light exposure levels and physical activity over 14 days at a sampling frequency of 50 Hz (50 readings per second). Participants were asked to wear the actiwatch continuously except for when showering or swimming, and to record the non-wear times (in the sleep diary). Data from the actiwatch were extracted and analysed using GENEActiv software to average the data in 60 s epochs. A correction factor was applied to the absolute illuminance values to obtain accurate light exposure levels recorded by the actiwatch.

#### Questionnaires for participant screening and, melanopsin function and chronotype/light timing determination

##### Addenbrooke's Cognitive Examination (ACE-III)

To assess the cognitive ability of the participants, the ACE-III questionnaire was administered by the examiner during the baseline (first) laboratory visit. The sum of the scores from all the sections of the questionnaire gave the ACE total score (range 1-100) which was used to determine the participant's eligibility; the higher the score, the better the cognitive abilities of the participant. The cut-off total score for participation in the study was  $\geq 82$ .

##### Determination of Melanopsin function (Post-illumination Pupil Response, 6sPIPR)

A Maxwellian-view pupillometer was used to measure the pupil light response to blue stimulus with high melanopsin (peak wavelength= 459 nm, full width at half maximum= 23 nm) and cone-dominated red stimulus with a low melanopsin excitation (peak wavelength= 632 nm, full width at half maximum= 16 nm) according to standard protocols. The lights were presented in a 50 degree central-retinal field (retinal image diameter = 20.1 mm) with a corneal irradiance of 15.5 log quanta.cm^-2.s. Pupillometry was completed at the beginning of each laboratory visit to minimize the time difference between repeats and the effect of circadian variation in pupil responses. Blink and lid artifacts in the raw pupil data were manually extracted and linearly interpolated using customized MATLAB software. Data were normalized to baseline pupil diameter and the 6s post illumination pupil response (PIPR) were quantified as % amplitude relative to the baseline pupil diameter.

### Morningness Eveningness Questionnaire (MEQ)

A hard copy of the MEQ questionnaire was administered during the first laboratory visit to assess the participant's chronotype to determine the timing of the supplemental light exposure. The sum of the scores from all 19 questions gave the MEQ total score (range 16-86) to determine whether the participant was a morning, evening or an intermediate type. Scores  $\leq 41$  indicate evening types; scores between 42-58 indicate intermediate types; scores  $\geq 59$  indicate morning types.

| Morningness-Eveningness Score                                                                                            | Start time for light therapy |
|--------------------------------------------------------------------------------------------------------------------------|------------------------------|
| 16-18                                                                                                                    | 8:45 AM                      |
| 19-22                                                                                                                    | 8:30 AM                      |
| 23-26                                                                                                                    | 8:15 AM                      |
| 27-30                                                                                                                    | 8:00 AM                      |
| 31-34                                                                                                                    | 7:45 AM                      |
| 35-38                                                                                                                    | 7:30 AM                      |
| 39-41                                                                                                                    | 7:15 AM                      |
| 42-45                                                                                                                    | 7:00 AM                      |
| 46-49                                                                                                                    | 6:45 AM                      |
| 50-53                                                                                                                    | 6:30 AM                      |
| 54-57                                                                                                                    | 6:15 AM                      |
| 58-61                                                                                                                    | 6:00 AM                      |
| 62-65                                                                                                                    | 5:45 AM                      |
| 66-68                                                                                                                    | 5:30 AM                      |
| 69-72                                                                                                                    | 5:15 AM                      |
| 73-76                                                                                                                    | 5:00 AM                      |
| 77-80                                                                                                                    | 4:45 AM                      |
| 81-84                                                                                                                    | 4:30 AM                      |
| 85-86                                                                                                                    | 4:15 AM                      |
| Recommended start time for light therapy based on Morningness-Eveningness Questionnaire (MEQ) score. |                              |

### Primary outcome measures

#### Polysomnography (PSG)

To measure human biological parameters while sleeping, such as brain activity via the electroencephalogram (EEG), rapid eye movements via the electrooculogram (EOG), limb movements via the electromyogram (EMG), electrocardiographic (ECG) and breathing patterns, an in-home polysomnography (PSG) device (Somte PSG, Compumedics Limited, Australia) was applied at the three time points. The PSG was set up by clinical trial staff to start recording ~ 1 hour prior to the participant's habitual bedtime. The set up included EEG electrodes (F4-M1, C4-M1, O2-M1 with contralateral backup), EOG electrodes (E1-M2, E2-M1), two electrodes placed on the inferior edge of each mandible and referenced to one on the middle of the chin for the EMG, one electrode placed between the 3rd and 4th rib and referenced to the electrode placed over the right collar bone for the ECG. Leg movements were recorded via two EMG electrodes placed 3cm apart on the middle of the anterior tibialis muscle on each leg. Breathing patterns and oronasal airflow was measured using a nasal cannula and a thermistor. All signals were collected at a sampling rate between 32-256 Hz with 16-bit resolution. Blood oxygen saturation was measured by an oximeter at 1 Hz. Input impedance was  $>20 \text{ M}\Omega$  (at 5Hz) for all PSG channels. Data were stored on a compact flash memory card. Recording continued until waking time the next morning. Participants were instructed on how to detach the instrument from their body upon waking the next morning, by themselves or with their partner's help. Data from the memory card was extracted to the review computer and analysed by an independent sleep scientist using Profusion sleep software (v5) (Compumedics Limited, Australia) and according to the American Academy of Sleep Medicine (AASM). High pass filters at 0.35Hz and low pass filters at 35Hz were used for the scoring of EEG signals. For scoring of EMG and limb channels, 10Hz high pass and 100Hz low pass filters were used.

**Outcome measures:** Sleep stages (N1, N2, N3, REM), Total sleep time, Sleep onset latency, Stage REM latency, Sleep efficiency, Time awake, Total PLMS Arousal Index

#### Dim Light Melatonin Onset (DLMO)

At each time point, seven saliva samples were collected in separate tubes (Salivettes, Sarstedt AG & Co, Adelaide, Australia) under dim light illumination ( $<30 \text{ lux}$ ) every hour starting 6 hours before habitual bedtime and ~ 1 hour

after bedtime at the participant's home. Participants were asked to write the time of the sample collection on a separate sheet of paper. Samples were stored in the participants freezer until collected the following day. The tubes were then stored in the laboratory at -60 degrees Celsius. Melatonin concentrations in each tube were determined by radioimmunoassay technique at the Adelaide Research Assay Facility.

The onset of melatonin was estimated using a skewed baseline cosine function (SBCF) model fitted to the seven (melatonin concentration) data points using customized MATLAB software.

The SBCF model is given as  $Y(t) = b + (H/(2*(1-c))) * (\cos(t-\phi + v * \cos(t-\phi)) - c + |\cos(t-\phi + v * \cos(t-\phi)) - c|)$

where  $t$  = time (radians),  $b$  = baseline salivary melatonin,  $H$  = height of the amplitude above baseline,  $c$  = width,  $\phi$  = phase (radians), and  $v$  = skewness (radians).

DLMO in decimal time (corresponding to 1% above threshold melatonin concentration levels of 4.3pM) were obtained from the model fitting.

**Outcome measures:** DLMO decimal time

### Key secondary outcome measures

#### Pittsburgh Sleep Quality Index (PSQI)

A hard copy of the PSQI questionnaire was provided at each time point to assess the participants night-time sleep quality and sleep disturbances. The sum of scores of all the 7 components gave the global PSQI score (range 0-21). The higher the global score, the worse the participant's quality of sleep.

The bed partner's (PSQI-BP) response on the participant's sleep behaviour was also calculated as the sum of 5 scores of the PSQI question 10 (range 0-15) in case a bed partner was present.

**Outcome measures:** PSQI total score (TS), PSQI bed partner reported sleep quality (PSQI-BP)

#### Parkinson's Disease Sleep Scale (PDSS)

A hard copy of PDSS questionnaire was provided at each time point to assess the participants' night-time sleep behaviour. The severity of sleeping difficulty was determined based on the responses to the 15 questions reported on a 0-10 scale (with 10 indicating the least difficulty in sleeping). The sum of scores from 15 questions gave the PDSS score (range 0-150), the higher the score the better the sleep behaviour. A maximum cumulative score of 150 indicated the participant had no sleeping difficulties at all.

**Outcome measure:** PDSS total score

